### Outcomes

#### Primary Efficacy Outcome

The changes of right ventricular stroke volume (RVSV) from baseline to Week 26 are determined by CMR. RVSV indexed for BSA is shown to predict outcome (22). RVSV quantifies blood flow independently of HR. An increase in RVSV reflects favorable, reverse remodeling of the right ventricle (RV) and is expected to reduce PAH symptoms through better oxygenation.

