### Adverse Events

Participants may voluntarily withdraw at any time, or if they experience a serious adverse event (SAE) that is associated with exercise training. All SAEs are discussed with the principal investigator who assesses seriousness and causality. Other adverse events (AEs), defined as any unfavorable and unintended sign, symptom or diseases, are also recorded. AEs are followed up until normalization, recovery or symptoms stabilize.

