### Statistical Analysis

Data will be presented as mean (SD), median (interquartile range), and frequency (percentage) available for data characteristics. For comparisons between groups, a *t*-test or rank-sum test will be applied for quantitative variables, while the χ^2^ test or Fisher's exact test for qualitative variables.

Primary and secondary endpoints will be analyzed using the whole population. However, patients who withdrew their consent, patients with severe protocol violations, or patients without the primary endpoint data, will be excluded from the whole population (26). An intention-to-treat analysis will be used to avoid, with inclusion of all available measures, regardless of whether participants completed the intervention, while the safety analysis will be done in the safety analysis population. Primary outcome analysis will be performed by an analysis of covariance (ANCOVA) model. Changes from baseline in RVSV will be analyzed using an ANCOVA with a factor for other PAH-specific therapies (none, background, or initiated at baseline) and a covariate for baseline RVSV. Missing outcomes were imputed as the multiple imputation. For analysis of categorical data, the McNemar–Bowden test will be used. *P* < 0.05 with two-sided test is considered statistically significant. All analyses will be performed with IBM SPSS V20 (IBM Corp., Armonk, NY, USA).

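### The efficacy population drops severe violators and patients without Week 26 data after randomisation, against the stated intention-to-treat analysis and multiple imputation

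*Protocol article*

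**What the plan says.** All the analysis rules stand in one paragraph of the protocol article, under Statistical Analysis:

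- Population: "Primary and secondary endpoints will be analyzed using the whole population".
- Exclusions from that population: "patients who withdrew their consent, patients with severe protocol violations, or patients without the primary endpoint data, will be excluded from the whole population".
- Principle: an intention-to-treat analysis, "with inclusion of all available measures, regardless of whether participants completed the intervention".
- Missing data: "Missing outcomes were imputed as the multiple imputation".
- Model: "Primary outcome analysis will be performed by an analysis of covariance (ANCOVA) model", with baseline RVSV as covariate.

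Only the safety population is set apart. The paragraph does not present the other rules as separate analysis sets and does not say which one is primary.

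Two other sections bear on the point. Primary Efficacy Outcome says: "The changes of right ventricular stroke volume (RVSV) from baseline to Week 26 are determined by CMR". Adverse Events says: "Participants may voluntarily withdraw at any time, or if they experience a serious adverse event (SAE) that is associated with exercise training".

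**The concern.** The exclusions depend on what happens after randomisation. A missing Week 26 scan can only arise then, and protocol violations naturally do too. There are several reasons why the two arms might lose different patients:

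- Only the training arm has a 12-week exercise programme to violate (Table 1).
- One named withdrawal route applies "if they experience a serious adverse event (SAE) that is associated with exercise training", which in practice belongs to the training arm.
- Patients know their allocation. Outcome assessors and CMR observers are blinded, but the article does not say whether whoever judges a violation to be severe is blinded.
- Study Design and Setting requires medication to stay unchanged. A patient who deteriorates and has treatment changed may therefore be counted as a violator.

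If patients who do badly are the ones removed, and at different rates by arm, the primary comparison is no longer between the groups that randomisation created. The conflict also leaves room to choose between two populations once the data have been seen.

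**Working it through.** **1. Do the rules fit together for the primary endpoint?**

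| Patient | Exclusion rule | Intention-to-treat rule | Imputation rule |
|---|---|---|---|
| Severe violation, Week 26 scan done | out | in | not needed |
| Stopped training, no Week 26 scan | out | in, as far as measured | in, by imputation |
| Withdrew consent | out | in, as far as data may be used | possibly in |

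The first row is a direct contradiction. In the second, the exclusion rule removes exactly the patients that imputation would serve, so for the primary endpoint it has nothing to act on.

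**2. How many patients are at issue?** Sample Size Calculation gives 77 per group, 20% dropout, and 96 per group (192 in total).

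- Dropout step: 77 / (1 − 0.20) = 96.25 and 154 / 0.80 = 192.5. The stated 96 and 192 reproduce to within rounding.
- Expected losses: 0.20 × 192 = 38.4 patients, leaving 153.6, or about 154. Violators who were scanned would come on top.
- The starting figure of 77 does not follow from 9 mL with SD 18–22 mL (the normal approximation gives 85 to 126 per group). That is a separate matter and does not bear on this point.

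**3. How large could the bias be?** Let e be the share of an arm that is removed, and k the amount by which the mean RVSV change of those removed is worse than that of the rest. The full-arm mean is (1 − e)m + e(m − k) = m − ek, so removal raises the arm mean by ek. The training-minus-control difference shifts by

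bias = e(T)·k(T) − e(C)·k(C).

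The article gives neither e nor k by arm, so the values below are assumptions.

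- Training arm only, e = 0.10, k = 15 mL: 0.10 × 15 = 1.5 mL, and 1.5 / 9 = 17% of the target.
- Range, training arm only: 0.05 × 10 = 0.5 mL to 0.15 × 20 = 3.0 mL.
- Equal removal, 10% and 15 mL in both arms: 1.5 − 1.5 = 0.
- More controls removed, 5% against 10%, both 15 mL: 0.75 − 1.5 = −0.75 mL, against training.

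**4. Effect on the type I error.** Assume no true effect, SD 20 mL (inside the stated 18–22), 96 randomised per group and removal from the training arm only. Then SE = 20 × √(1/96 + 1/(96(1 − e))), and the two-sided error is P(Z > 1.96 − bias/SE) + P(Z < −1.96 − bias/SE). For e = 0.10 and k = 9: SE = 20 × √(1/96 + 1/86.4) = 2.97, bias/SE = 0.9 / 2.97 = 0.30, and the error is 0.061.

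| Removed | Worse by | Shift | Type I error |
|---|---|---|---|
| 5% | 9 mL | 0.45 mL | 0.053 |
| 10% | 9 mL | 0.9 mL | 0.061 |
| 20% | 9 mL | 1.8 mL | 0.090 |
| 20% | 18 mL | 3.6 mL | 0.22 |

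**5. Effect on power.** At 9 mL and SD 18/20/22 mL, power is 0.87/0.80/0.72 with 77 per group and 0.93/0.88/0.81 with 96. The second set is an upper bound, because imputation does not restore lost information.

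**The case against.** The best defence is that the clash is narrower than three incompatible rules. Intention to treat is described here in terms of available measures, which could tolerate leaving out patients with no Week 26 scan. Imputation might be meant for secondary outcomes or a missing baseline. A patient who stops training but is scanned is kept by the intention-to-treat sentence. Excluding patients who refuse use of their data is defensible. A separate analysis plan may name the primary set.

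These readings do not rescue the paragraph. It applies the exclusions expressly to the primary endpoint, does not limit imputation to other outcomes, and still removes severe violators who have scans. This is a conflict in what the article states, not a detail left to another document.

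The objections to the size carry more weight:

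- Both e and k are assumed, and the 20% dropout says nothing about imbalance between arms.
- Voluntary withdrawal is open to both arms, and the text does not say whether withdrawal after an SAE is from training or from follow-up.
- No passage defines a medication change as a severe violation. If it counted as one, deteriorating controls would be removed too, which pulls the other way.
- Imputation removes bias from missing scans only if the variables in the imputation model explain why they are missing.

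So the direction and size are unknown. The contradiction is not.

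**Conclusion.** The concern holds. As written, the paragraph would exclude randomised patients from the primary analysis on post-randomisation grounds, while promising an analysis that keeps them and an imputation that the exclusions make redundant for RVSV. The resulting comparison can be biased. With removal only from the training arm, the assumed ranges give 0.5 to 3.0 mL, or 6% to 33% of the 9 mL target (0.5 / 9 and 3.0 / 9). The bias is zero if exclusion is unrelated to outcome, or equally selective in both arms, and can run against training if controls are lost more selectively. Because the conflict concerns the analysis set for the primary endpoint and the plan itself expects about 38 losses, it must be fixed before the data are analysed.

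**What to change.** - Define the primary analysis set as all randomised patients in their assigned group, regardless of adherence, protocol violation or medication change. This settles whose data are analysed. It sets no rule for treatment.
- Multiply impute missing Week 26 RVSV separately by arm, using baseline RVSV, sex, 6MWD and NT-proBNP. Table 2 marks no NT-proBNP measurement at preterm termination, so for early leavers only the baseline value may be available.
- Because imputation rests on an untestable assumption about the missing scans, add a sensitivity analysis that makes the imputed values progressively worse, by arm.
- Move the set with exclusions to a labelled per-protocol sensitivity analysis, and define a severe violation before allocation is known to those who classify it.
- State that stopping training is not leaving the trial, and that the Week 26 CMR is sought for every patient who has not withdrawn consent for follow-up.

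The cost is a change of wording, plus some effort to bring back patients who stop training for a scan that is already planned. The design and the planned number of patients do not change.

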## Methods And Analysis

### Study Design and Setting

The study of the efficacy and safety of aerobic exercise training in PAH (the Saturday study) will recruit subjects from 1 June 2020 to 1 June 2023. The study is a 26-week multicenter, prospective, and RCT. Subjects willing to consider enrollment will be consented. Patients with PAH stable on PAH-targeted drugs for at least 3 months prior to inclusion are randomly assigned to the control and training groups. Medication remains unchanged during the study period (Figure 1). We will use the SPIRIT checklist and TIDiER checklist when writing our report (Supplementary Materials 1, 2) (17, 18). All centers will follow a standardized protocol, including rehabilitation, diagnosis, and evaluation of PAH, as shown in Table 1.

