### Eligibility Criteria

#### Inclusion Criteria

(a) Group 1 PAH (idiopathic, heritable, drugs, connective tissue diseases, or all kinds of congenital heart diseases) based on the diagnostic criteria of the 6th World Symposium on Pulmonary Hypertension (19); (b) age ≥ 18 or <60 years, (c) World Health Organization functional class (WHO FC) II or III, (d) stable and compensated under PAH-targeted medications, diuretics, and supplemental oxygen for at least 3 months; (e) willing to sign written informed after full explanation of this study; (f) 6-min walking distance (6 MWD) ≥ 200 m.

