### Allocation Concealment and Blinding

A computer-generated, permuted-block randomization sequence were applied for allocation with two block sizes. The patients are randomized to the control group or receive exercise training group in a 1:1 ratio (stratification by sex). The sequence is concealed in an opaque envelope until the intervention is assigned. Patients cannot be blinded to the outcome of randomization, Furthermore, to increase the robustness of the outcomes, outcome assessors are blinded to the outcome of randomization.

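### The primary ANCOVA leaves out sex, the only stratification factor, and adjusts for a therapy factor with at least one level that the eligibility rules exclude

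*Protocol article*

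**What the plan says.** All references are to the protocol article.

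- **Primary model (Statistical Analysis).** The method is fixed: "Primary outcome analysis will be performed by an analysis of covariance (ANCOVA) model". The terms follow in the next sentence: "Changes from baseline in RVSV will be analyzed using an ANCOVA with a factor for other PAH-specific therapies (none, background, or initiated at baseline". The only other term listed is baseline RVSV, entered as a covariate.
- **Other comparisons (same section).** A general sentence reads: "For comparisons between groups, a *t*-test or rank-sum test will be applied for quantitative variables".
- **Randomisation (Allocation Concealment and Blinding).** Patients are allocated "in a 1:1 ratio (stratification by sex"). No other stratification factor is given.
- **Eligibility (Inclusion Criteria, item d).** Patients must be "stable and compensated under PAH-targeted medications, diuretics, and supplemental oxygen for at least 3 months".
- **Conduct (Study Design and Setting).** "Medication remains unchanged during the study period". The Abstract describes drug treatment in the same way, and the Discussion names as a possible limitation that drug treatment was held fixed because of the study.

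**The concern.** The article does more than name a method: it lists the model terms. Three features of that list do not fit the design.

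1. Sex is absent although allocation is balanced on it. When a stratifier is prognostic, a model that ignores it reports a standard error that is too large, because the balance achieved by design is not credited in the analysis.
2. The single factor that is included describes a population with untreated patients, patients on background therapy and patients starting therapy at baseline. The eligibility and conduct rules describe a population in which everyone is on stable background therapy.
3. The term that carries the treatment comparison is not written down.

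This is the only primary analysis of the only primary endpoint. At stake are some precision and a model statement that can be followed without guessing. If the model is settled only after the data are seen, the choice of adjusters is open to question.

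**Working it through.** The plan gives no figure for the effect of these model terms, so there is none to reproduce. The check has two parts.

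**A. Therapy factor against eligibility**

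| Level | Ordinary reading (any PAH drug) | Alternative reading (drugs beyond a first one) |
|---|---|---|
| *none* | excluded: inclusion requires stable PAH-targeted medication | possible: patients on one drug |
| *background* | required of everyone | possible |
| *initiated at baseline* | excluded by 3 months' stability and unchanged medication | excluded for the same reason |

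On the ordinary reading every eligible patient is in *background*. The design matrix then has 4 columns (intercept, two therapy indicators, baseline RVSV), but both indicators are zero for everyone and the rank is 2. The factor drops out. It uses no degrees of freedom and causes no bias, but it adjusts for nothing.

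**B. Cost of omitting sex, with a group term in the model**

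If sex explains a fraction f of the variance left after group and baseline RVSV, the standard error of the group effect is too large by the factor √(1/(1 − f)). The documents give no value for f, so 5% to 10% is an assumed range.

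- f = 0: √(1/1.00) = 1.000, no effect
- f = 0.05: √(1/0.95) = 1.026, 2.6% too large
- f = 0.10: √(1/0.90) = 1.054, 5.4% too large

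A simulation gives the same picture. Inputs from Sample Size Calculation: 154 patients, a difference of 9 mL, and an SD of 18 mL (the lower end of the stated 18–22 mL, used as the residual SD). Assumed: 70% women, and a sex effect in units of that SD. Allocation was balanced within sex; there were 4,000 replicates per setting, and both models contained group and baseline RVSV.

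| Sex effect (assumed) | Type I error, without / with sex | Power, without / with sex |
|---|---|---|
| 0 | 0.049 / 0.049 | 0.876 / 0.875 |
| 0.3 SD | 0.053 / 0.055 | 0.869 / 0.873 |
| 0.5 SD | 0.046 / 0.052 | 0.854 / 0.865 |
| 0.8 SD | 0.038 / 0.052 | 0.833 / 0.863 |

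With 70% women, a sex effect of d SDs explains f = 0.21d²/(1 + 0.21d²), since 0.7 × 0.3 = 0.21. For d = 0.5 this is 0.0525/1.0525 = 5.0%; for d = 0.8 it is 0.1344/1.1344 = 11.8%. The simulated settings therefore run from zero to slightly beyond the assumed range. Simulation error at a rate of 0.05 is √(0.05 × 0.95/4,000) = 0.003, so only the 0.038 lies clearly away from 0.05, and it lies on the conservative side. The largest power loss is 0.863 − 0.833 = 0.030.

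The power without a sex effect (about 0.875) reflects the chosen 9 mL and 18 mL with 77 per group. Its distance from the planned 90% is a separate sample-size question.

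**The case against.** **Group term.** A reader might infer that the primary analysis, followed literally, estimates no treatment effect. The documents do not support that. The trial is a 1:1 randomised comparison, the sample size is set per group, and an article that lists only the adjusters of an ANCOVA commonly leaves the group term implicit. Nor does the general sentence on t-tests and rank-sum tests displace the ANCOVA, which is named specifically for the primary outcome. What stands is that the terms are enumerated and group is not among them, so naming it is a fair clarification.

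**Therapy factor.** A reader might infer that all of its levels are impossible, or that it damages the analysis. Neither holds. *Background* is exactly what eligibility requires, and a constant factor does no numerical harm. The word *other* has no clear referent when the intervention is exercise, so *none* could be populated under the alternative reading. What stands is that *initiated at baseline* conflicts with the eligibility and conduct rules on either reading.

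**Sex.** The documents give no effect of sex on change in RVSV once baseline RVSV is in the model, and zero is compatible with them. The error is conservative and small. This objection stands as to size. It does not remove the mismatch between how patients are randomised and how they are analysed, and that costs almost nothing to correct.

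**Conclusion.** The point holds in a limited form. The stated primary model omits the only stratification factor, and its one factor has a level (two, on the ordinary reading) that conflicts with the requirement for stable, unchanged medication. With eligibility met, the factor is probably constant; that conclusion rests on reading *other PAH-specific therapies* as any PAH drug. The unnamed group term is a gap in drafting and does not show that no comparison is planned.

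Omitting sex leaves type I error at or below its nominal level, within simulation error. The standard error is too large by 2.6% to 5.4% if sex explains 5% to 10% of residual variance, and by nothing if sex is not prognostic given baseline RVSV. The simulated power loss is about 1 percentage point at an assumed 0.5 SD sex effect and about 3 at 0.8 SD. These sizes are illustrative. The case for change rests on the mismatch with the design and on the low cost of removing it.

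**What to change.** Replace the model sentence in Statistical Analysis with: change in RVSV at Week 26 = randomised group + sex + baseline RVSV, reporting the adjusted mean difference (training minus control) with its 95% confidence interval and two-sided p-value.

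Reconcile the therapy factor with Inclusion Criteria and Study Design and Setting in one of two ways: remove it, or redefine it by categories of background therapy that can occur among eligible patients. Either resolves the inconsistency, and the choice is the trial team's.

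The cost is about one sentence and one degree of freedom for sex. Sex is known at randomisation, baseline RVSV is already in the model, and the planned medication records could supply background-therapy categories. The sample size does not change. The revision should be made and dated before the outcome data are analysed.

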#### Secondary Efficacy Outcome

In the same method as that used for the primary endpoints, secondary endpoints are assessed at 26 weeks. They consist of characteristics of the RV, and of widely accepted tools to assess PAH progression:

RV end diastolic volume (RVEDV),RV end systolic volume (RVESV),RV ejection fraction (RVEF),RV mass,WHO FC,6 MWD, andN-terminal pro-B-type Natriuretic peptide (NT-proBNP).

Variables pertaining to the left ventricle (LV) are also assessed.

Changes from baseline to Week 26 in:

LV SV,LV end diastolic volume (LVEDV),LV end systolic volume (LVESV),LV ejection fraction (LVEF),LV mass,RVEDV/LVEDV, andRVESV/LVESV.

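### Two kinds of test are named for categorical data; the one in the endpoint paragraph is a paired test that cannot compare training with control on WHO functional class

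*Protocol article*

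**What the plan says.** All of the analysis text is in the Statistical Analysis section of the protocol article, in two paragraphs.

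- **First paragraph.** After the descriptive statistics comes a generic rule that begins "For comparisons between groups, a" and gives t-test or rank-sum for quantitative variables and, for categorical ones, χ² "test or Fisher's exact test for qualitative variables". It is not limited to baseline data.
- **Second paragraph.** It opens with "Primary and secondary endpoints will be analyzed using the whole population", goes on to the ANCOVA for right ventricular stroke volume (RVSV) and to multiple imputation, and then states: "For analysis of categorical data, the McNemar–Bowden test will be used". The significance rule follows directly: P "< 0.05 with two-sided test is considered statistically significant".

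Under Secondary Efficacy Outcome, "secondary endpoints are assessed at 26 weeks". WHO functional class is on that list and is the only clearly categorical item; the inclusion criteria restrict it to class II or III at entry. Under Allocation Concealment and Blinding: "The patients are randomized to the control group or receive exercise training group in a 1:1 ratio (stratification by sex". That section also says that patients cannot be blinded.

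**The concern.** A McNemar-type test cross-tabulates each patient's class before and after and asks whether moves up and moves down are equally frequent. Treatment group does not enter. It can be run in one arm or in both arms pooled, but neither version estimates the difference between randomised groups.

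The sentence stands where a reader looks for the endpoint analysis, and nothing in it says within-arm, supplementary or descriptive. The second paragraph replaces the generic t-test by ANCOVA for RVSV, so it is natural to read it as replacing χ²/Fisher by the McNemar-type test for categorical endpoints.

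What is at stake is the WHO functional class result. Class can improve in both arms of an unblinded trial through expectation or regression to the mean. A significant change in the training arm, with or without one in the control arm, could then be presented as a training effect although the arms do not differ. With two tests of different null hypotheses on the page, the choice could also be made after the data are seen.

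**Working it through.** The plan gives no figure that rests on this choice, so there is none to reproduce. The check has two parts.

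**1. What each test can answer**

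| | χ² / Fisher (first paragraph) | McNemar–Bowker (second paragraph) |
|---|---|---|
| Data | two independent samples | paired before/after classes |
| Null hypothesis | same distribution in both arms | moves between each pair of classes are symmetric |
| Group term | yes | none |
| Stated purpose | between-group comparison | not stated |

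The arms are independent, so only the first column addresses the randomised question.

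**2. Illustration of the consequence**

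Inputs:
- n = 77 per arm (Sample Size Calculation, before the dropout allowance).
- α = 0.05, two-sided (Statistical Analysis).
- Improve and worsen rates: the article gives none. They are assumed, are the same in both arms (no training effect), and are varied.

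With b improved and c worsened in an arm, the uncorrected McNemar statistic is (b − c)²/(b + c) on 1 df. This treats class change as improved or worsened, which is Bowker's test when only two classes are in play.

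*Single example.* Let 20 improve and 8 worsen of 77 in each arm.
- Within each arm: (20 − 8)²/(20 + 8) = 144/28 = 5.14, p = 0.023.
- Between arms, proportion improved: 20/77 against 20/77, χ² = 0, p = 1.00.

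Both arms are significant and there is no difference between them.

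*Long-run rates.* Let r be the probability that the paired test is significant in one arm, obtained by summing multinomial probabilities over all (b, c) with (b − c)²/(b + c) > 3.84. The arms are independent and identical, so the probability that training is significant and control is not is r(1 − r). The last column is the between-arm χ² on the proportion improved.

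| Improve / worsen, both arms | Training arm significant, r | Training yes, control no, r(1 − r) | Pooled arms significant | Between-arm χ² |
|---|---|---|---|---|
| 10% / 10% | 5% | 0.048 × 0.952 = 5% | 5% | 5% |
| 15% / 10% | 14% | 0.144 × 0.856 = 12% | 23% | 5% |
| 20% / 10% | 37% | 0.374 × 0.626 = 23% | 63% | 5% |
| 20% / 8% | 54% | 0.536 × 0.464 = 25% | 82% | 5% |

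The third column cannot exceed 25%, the maximum of r(1 − r). The exact form of McNemar's test is more conservative: at 20%/8%, r is about 43–44% and the third column about 24%.

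*The reverse failure.* If training truly improves class (25% improve, 10% worsen) and control truly worsens (10% improve, 25% worsen), the moves cancel on pooling. In simulation, the pooled paired test rejects in about 4% of trials and the between-arm χ² in about 71%.

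**The case against.** A reader might infer that WHO functional class is definitely assigned a paired test and that the plan has no between-arm test for it. The text does not support that. The McNemar sentence never mentions functional class; the link comes from the endpoint list. The same section names χ²/Fisher for comparisons between groups and does not confine it to baseline. A coherent plan can be read out of this: χ²/Fisher compares the arms, and McNemar–Bowker describes change within each arm. Tests that answer different questions do not conflict, and on that reading nothing is wrong except the test's name. This much stands, and it makes the defect an ambiguity and not a certain error.

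The size also depends on assumptions. With no net drift (10%/10%) nothing is inflated. The single-arm and pooled percentages are largely correct detection of a before–after change that was put into the calculation; they become false positives only if presented as a training effect, which the article does not say it will do.

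Finally, χ² between randomised arms is valid. That it ignores the ordering of classes and the baseline class is a point about efficiency, and model detail for one secondary endpoint is often left to an analysis plan.

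What remains is that the article positively states a test in its endpoint paragraph, gives it no limiting purpose, and that test cannot answer the randomised question.

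**Conclusion.** The point holds as an ambiguity with a real risk. The Statistical Analysis section names two kinds of test for categorical data and does not say which gives the training-versus-control comparison of WHO functional class. If the McNemar-type test is used for it, as its placement suggests but does not establish, the training effect on that endpoint goes untested.

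Under identical arms and assumed change rates, a pattern that looks like benefit (training significant, control not) would appear in about 5% to 25% of trials, depending on how far both arms drift, against about 5% for a between-arm test. The range rests on 77 evaluable patients per arm, the uncorrected test, assumed rates and a within-arm result being taken as an arm contrast.

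One secondary endpoint is affected. The RVSV analysis by ANCOVA is not. The change should be made, but it does not threaten the trial's main conclusion.

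**What to change.** Replace the McNemar sentence with wording such as: *WHO functional class at Week 26 will be compared between the randomised groups by proportional-odds logistic regression with terms for group, baseline WHO functional class and sex; the common odds ratio and its 95% confidence interval will be reported. If cells are too sparse, a Cochran–Mantel–Haenszel row-mean-score test stratified by baseline class will be used. Within-arm change may be described with the McNemar–Bowker test and will not be used to infer a training effect.*

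The minimum repair is to state that the χ²/Fisher test already named gives the arm comparison and that McNemar–Bowker is descriptive. Either way, correct the test's name.

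The cost is a short text change before the data are analysed. Baseline class and sex are already collected (sex is the stratification factor), and neither sample size nor visits change. Check that the named software package offers the row-mean-score test before writing it in as the fallback.
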